# Investigating the effect of intra-operative infiltration with local anaesthesia on the development of chronic postoperative pain after inguinal hernia repair. A randomized placebo controlled triple blinded and group sequential study design [NCT00484731]

**DOI:** 10.1186/1471-2482-7-22

**Published:** 2007-11-06

## Abstract

**Background:**

Inguinal hernia repair is one of the most frequently performed procedures in Switzerland (15'000/year). The most common complication postoperatively is development of chronic pain in up to 30% of all patients irrespective of the operative technique.

**Methods/Design:**

264 patients scheduled for an inguinal hernia repair using one of three procedures (Lichtenstein, Barwell and TEP = total extraperitoneal hernioplasty) are being randomly allocated intra-operatively into two groups. Group I patients receive a local injection of 20 ml Carbostesin^® ^0.25% at the end of the operation according to a standardised procedure. Group II patients get a 20 ml placebo (0.9% Saline) injection. We use pre-filled identically looking syringes for blinded injection, i.e. the patient, the surgeon and the examinator who performs the postoperative clinical follow-ups remain unaware of group allocation. The primary outcome of the study is the occurrence of developing chronic pain (defined as persistent pain at 3 months FU) measured by VAS and Pain Matcher^® ^device (Cefar Medical AB, Lund, Sweden).

The study started on July 2006. In addition to a sample size re-evaluation three interim analyses are planned after 120, 180 and 240 patients had finished their 3-months follow-up to allow for early study termination.

**Discussion:**

Using a group sequential study design the minimum number of patients are enrolled to reach a valid conclusion before the end of the study.

To limit subjectivity, both a VAS and the Pain Matcher^® ^device are used for the evaluation of pain. This allows us also to compare these two methods and further assess the use of Pain Matcher^® ^in clinical routine.

The occurrence of chronic pain after inguinal hernia repair has been in focus of several clinical studies but the reduction of it has been rarely investigated. We hope to significantly reduce the occurrence of this complication with our investigated intervention.

**Trial Registration:**

Our trial has been registered at ClinicalTrials.gov. The trial registration number is: [NCT00484731].

## Background

Inguinal hernia repair is one of the most frequently performed procedures in Switzerland (about 15'000 cases per year) [1]. The most common complication postoperatively is development of chronic pain in up to 30% of patients irrespective of the operative technique [2-7]. Callesen et al. [3] found the persistence of pain at 1 and 4 weeks after surgery to be a predictive factor on the development of chronic pain. Courtney et al. [8] concluded that chronic pain persists in most patients who report pain up to 3 months after hernia repair. Surgical procedures like the ilioinguinal neurectomy recently described by Mui et al. [9] lead to a significant reduction of chronic pain but also to numbness and discomfort in the groin region. Whereas Ravichandran et al. [10] in contrast showed no significance of the elective division of the ilioinguinal nerve.

In addition to the problems caused by hernia surgery the objective evaluation of the postoperative pain is limited. The Visual Analogue Scale (VAS) is often used in similar study settings and is well known as "gold standard" for eliciting pain. However Lundeberg et al. [11] reported the VAS is a questionable instrument for the measurement of pre- and postoperative pain because it remains very subjective and is based on varying previous pain experience. Hence the VAS has a misleading precision because of an imprecise individual determination of the VAS of about ± 20 mm (DeLoach et al.) [12].

An alternative option for measuring pain is the recently developed Pain Matcher^® ^by Cefar Medical AB, Lund, Sweden. This perceptual matching device uses electrical stimulation against which the patient has to match the perceived pain with nonvisualized endpoints. It seems to be more objective and reduces recording bias. The device has been tested for safety and reliability in several clinical trials [13-16] and has not been used so far in the field of hernia surgery.

The use of local compared to general anaesthesia in hernia surgery has only been described by O'Dwyer et al. [17] not investigating the outcome on the development of chronic pain after hernia repair. A positive effect of postoperative single shot or continuous infiltration with local anaesthetics on acute postoperative pain has been described by several authors [18-20].

We designed a randomized placebo controlled triple blinded trial to investigate the effect of an additional intra-operative infiltration with local anaesthesia on the development of chronic postoperative pain. Because of incertainty of data used for sample size estimation, a sequential design data analysis for early study stopping along with revision of sample size is applied. As Aasvang and Kehlet [21] pointed out there is an urgent need for the treatment opportunities and assessment of chronic pain after herniorrhaphy. We hope to contribute with this study to this common problem after hernia repair.

## Methods/Design

Patients are recruited in the outpatients and the emergency department. If they meet the inclusion criteria (see next section), informed consent is obtained and the operation is planned. According to our randomization process the patient is automatically either allocated to the verum or control group by the sequence of the consecutive numbered and block randomized syringes. An overview of the patient recruitment and follow-up is presented in Figure 1.

**Figure 1 F1:**
[figure not shown]
patient flow according to the revised CONSORT-statement.

### Inclusion and exclusion criteria

Adult patients (≥ 18 years) with primary or recurrent single or double sided symptomatic but not incarcerated inguinal hernias with an elective hernia repair are included. No other interventions (i.e. umbilical hernia) are allowed. Written informed consent needs to be obtained.

Patients with legal incompetence, pregnant and nursing women, patients with presence or history of active malignancy or systemic diseases, under immunosuppressive treatment, with systemic or severe local inflammation or infection, with wound healing disorders and with physical or mental incapacity, which makes it impossible to obtain informed consent are excluded. As pacemakers interfere with the electrical stimulation of the Pain Matcher^® ^and vice versa patients with pacemakers or other implanted electrical devices were also excluded.

### Surgical Methods

Allowed standardized surgical procedures for the hernia repair are Lichtenstein [22,23], Barwell [24] and TEP [25]. These procedures for the hernia repair are performed directly or under the supervision by used to test the efficacy of the local infiltration. The operation is performed by a general surgery consultant or, a senior resident or under supervision of one of them. The hierarchical position and individual surgeon experience in the field of regarding inguinal hernia repair (i.e. number of performed operations) is documented.

### Anaesthesiological Methods

After the repair of the inguinal hernia the verum *Bupivacain *(Carbostesin^® ^0.25%) or the placebo *Saline *(0.9 %) is injected close to the nerves of the groin region following a standardized procedure (Figure 2). The injection starts 2 fingers below and 2 fingers medial the spina iliaca anerior superior on the lateral end of the incision (Figure 3). Ten ml of the substance will be injected fan-shaped laterally and 4 ml medially of the cranio-lateral puncture. The medio-caudal puncture is located directly above the pubic tubercle on the medial end of the incision. 4 ml of the substance will be fan-shaped injected lateral and 2 ml medial of the puncture.

**Figure 2 F2:**
[figure not shown]
anatomy of the groin region.

**Figure 3 F3:**
[figure not shown]
guide for the injection of the verum/placebo.

### Randomization & Blinding

The randomization based on a computer-generated block randomization sequence is performed in 1:1 ratio between the investigational and the control arm. The pharmacy of our hospital provides equal looking syringes of placebo and verum numbered according to the randomization sequence that is kept confidential. Patient, surgeon and the doctor performing examinations during follow-up visits will not know about treatment allocation for each patient, which leads to this unique triple blinded study design.

The randomization code will be broken only in the following circumstances:

- for all patients at the completion of the final data analyses

- for individual patients following the occurrence of adverse events requiring immediate knowledge of treatment allocation for the safety of the patient.

### The Pain Matcher Device

The Pain Matcher^® ^(Cefar Medical AB, Lund, Sweden; Figure 4) is a perceptual matching device unit that gives constant current stimulation which is controlled by a microprocessor that provides rectangular pulses with a frequency of 10 Hz and an amplitude of 10 mA. It is programmed to give a constant current stimulation despite variable skin resistance (e.g., influenced by sweating and anxiety of the subject) up to 13 kΩ. The intensifying of stimulation is achieved by successively increasing the pulse width from 0 to a possible maximum of 450 μs in increments of 7.5 μs, up to a total of 60 steps. The electrical charge per second is extremely low and varies through the different steps from 1.5 to 45 μC. The reached value (0–100) is directly related to the pulse width and is displayed on a liquid crystal display screen. The contact surface area, and hence the resulting current density, is ensured by a certain minimum finger pressure against the electrode; this is achieved by instructing the patient to hold the electrode box between the thumb and the index finger in a horizontal position requiring a certain minimum, predetermined pressure. A further increase in electrode pressure does not improve the functionality of the Pain Matcher^®^.

**Figure 4 F4:**
[figure not shown]
Pain Matcher^®^

### Primary Outcome

According to Courtney et al. [8] who concluded that chronic pain persists in most patients who report persistent pain at 3 months after hernia repair, we chose the occurrence of chronic pain (persistent pain at 3 months FU measured by VAS and Pain Matcher^®^) in the operated groin region for our primary outcome.

### Secondary Outcomes

#### Level of Pain

- Pain Matcher^®^

- VAS

- Areas of hyperalgesia, hypaesthesia

#### Hospitalization

- Length of stay (days)

- ASA-Classification

- Beginning of mobilisation (days)

- Removal of drainage (days)

#### Function

- Return to work or normal activity (days and %)

- Quality of life (SF36)

Amounts of follow-up and recorded parameters are summarized in Table 1.

**Table 1 T1:** Follow-up and recording of data

	**Baseline**		**FU 1**	**FU 2**	**FU 3**	**FU 4**
	Consultation	Intra-/post-OP	2 weeks	1 month	3 months	12 months
**General data**						
- Patients data						
- Informed consent						
**Anaesthesiological data**						
**Surgical intervention**						
**Edverse events**						
Primary outomes:						
- VAS						
- Pain Matcher^®^						
Secondary outcomes:						

### Hypothesis

We hypothesise a 50% reduction of the occurrence of postoperative chronic pain after 3 months in the intervention group receiving intra-operative infiltration with local anaesthetic after an inguinal hernia repair compared with patients in the control group receive placebo infiltration.

### Sample size & power calculation

Required sample sizes and interim analysis data for both groups were estimated using the computer programme East^® ^Version 4 (Cytel Inc., [name]). Sample size estimation was based on a risk of occurrence of chronic pain without local anaesthetic infiltration of 30% in patient having inguinal hernia surgery (Poobalan et al. [4]).

Considering a 0.05 two-sided significance level, a power of 80%, a detectable risk reduction of 50% and an allocation ratio of 1:1, 120 patients per group were estimated.

Assuming a dropout rate of 10% (declining, exclusion, loss to follow-up, etc.) in the study, ***132 patients per group***(264 patients) are going to be enrolled.

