### Group sequential design and interim analysis

To allow for early stopping of the trial, a group sequential analysis is performed. The first of three interim analyses will be performed as soon as 120 patients (60 per group) have had their 3-month follow-up. Further interim analyses are planned after 180 and 240 patients (final analysis).

We will use a χ^2^-test to test the null-hypotheses. The analysis will be performed on the 'intention-to-treat' basis, i.e. patients will be analyzed in the groups to which they were randomized.

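### Minor arithmetic error: a 10% dropout allowance added as 120 × 1.10 = 132 per group, where keeping 120 evaluable needs 120/0.90, i.e. 134

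*Protocol article*

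**What the plan says.** The section on sample size and power sets the design values: "Considering a 0.05 two-sided significance level, a power of 80%, a detectable risk reduction of 50% and an allocation ratio of 1:1", with a control-group risk of 30%. This gives 120 patients per group. The next step is "Assuming a dropout rate of 10% (declining, exclusion, loss to follow-up, etc.) in the study", which leads to 132 per group, and so "264 patients) are going to be enrolled". The abstract says that these 264 patients are the ones randomly allocated during the operation.

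The analysis times are counted in completers. According to the abstract, "three interim analyses are planned after 120, 180 and 240 patients had finished their 3-months follow-up". The section on the group sequential design and Table 2 both label the look at 240 as the final analysis, and Table 2 gives it a critical value of 2.0141 (p ≤ 0.044). The same section specifies intention-to-treat in the sense that "patients will be analyzed in the groups to which they were randomized". A sample size re-estimation is planned before the first interim analysis, and the stopping rules set a maximum of 200 per arm.

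**The concern.** An allowance for dropout should leave the required number after the loss has occurred. Multiplying by 1.10 adds 10% of the smaller, evaluable number. The loss, however, is taken from the larger, enrolled number, so the result falls slightly short. Here the shortfall lands on a figure that the design uses a second time: 240 is both the evaluable total behind the stated 80% power and the completer count that defines the last look. With the plan's own enrolment and dropout figures, the expected number of completers lies just below that count.

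At stake are the accuracy of the stated power, and a final look fixed at a completer count that the enrolment target does not quite support. The boundary of 2.0141 is printed for exactly 240 patients, and the actual number will almost certainly differ in one direction or the other.

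**Working it through.** **Inputs.** Two-sided alpha 0.05, power 80%, control risk 30%, 50% relative reduction (hence 15%), 1:1 allocation, 120 per group, dropout 10%, enrolment 132 per group (all from the sample size section); looks at 120, 180 and 240 with critical values 2.9626, 2.359 and 2.0141 (Table 2).

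**1. Reproducing 120 per group.** The fixed-sample formula for two proportions gives 121 with pooled variance and 118 with unpooled variance. With the Table 2 boundaries and 120 per group, overall two-sided type I error is 5.00% and power is 80.0% (unpooled) or 78.7% (pooled). The stated 120 is sound.

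**2. Reproducing 132.** 120 × (1 + 0.10) = 132, exactly the stated figure.

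**3. Correct inflation.** n/(1 − d) = 120/0.90 = 133.3, so 134 per group and 268 in total. The difference is 2 per group, 4 in total (4/264 = 1.5%).

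**4. Expected completers, if the 10% applies to those randomised.**
- 264 × 0.90 = 237.6 (118.8 per group), which is 2.4 below 240.
- 268 × 0.90 = 241.2.
- 264 enrolled yield 240 only if dropout is at most 1 − 240/264 = 9.1%.

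**5. Chance of reaching 240.** With an independent 10% dropout risk per patient, the binomial probability of at least 240 completers is 36% with 264 enrolled and 64% with 268.

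**6. Power.** Keeping the first two looks at 120 and 180 and moving the last to 237.6, group-sequential power is 79.6% against 80.0% at 240 (unpooled), or 78.3% against 78.7% (pooled). The loss is about 0.4 points.

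**7. Last boundary at other counts.** The table gives type I error when the printed 2.0141 is used in one final test after the looks at 120 and 180, and the critical value that restores 5%.

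| Final count | Type I error with 2.0141 | Critical value for 5% |
|---|---|---|
| 238 | 4.98% | 2.0125 |
| 240 | 5.00% | 2.0141 |
| 250 | 5.07% | 2.0215 |
| 264 | 5.15% | 2.0307 |

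A count of 250 corresponds to dropout of about 5%, and 264 to none.

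**The case against.** The best defence is that the error is too small to matter. Two patients per group cost about 0.4 points of power, while the choice between pooled and unpooled variance moves power by 1.3 points (80.0% − 78.7%). The article concedes that its sample size inputs are uncertain and plans a re-estimation before the first look, so 264 is a provisional target. This stands, and it fixes the point as minor. It does not make 132 the right result of the stated calculation.

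A second defence concerns the base of the 10%. The listed reasons include declining and exclusion, and allocation takes place during the operation. If some of these losses precede randomisation, the shortfall among randomised patients shrinks or vanishes. This stands as an assumption to be stated. The abstract favours the other reading, since it describes the 264 as randomly allocated.

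Three stronger conclusions are tempting, and the article does not support them:

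- A reader might infer that the final analysis can never be triggered. The shortfall holds only in expectation at 10% loss; 240 is still reached with about 36% probability, and re-estimation may change both the target and the looks.
- A reader might infer that completers beyond 240 are left out, against intention-to-treat. No sentence excludes them. The article is silent on their handling, and such detail may sit in an analysis plan that is not shown.
- A reader might infer a further test at 264 after the one at 240, because the abstract counts 240 among the interim analyses. That four-look procedure would have a type I error of 6.2% with 2.0141 used again, but the plan does not contain it. The design section and Table 2 both mark 240 as final, so the abstract's wording is loose naming.

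**Conclusion.** The dropout inflation is wrong as arithmetic: 132 per group should be 134, or the evaluable number should be stated as about 238. The effect is minor, with 4 patients too few in total and power of about 79.6% instead of 80.0%. This rests on 10% loss among randomised patients, risks of 30% and 15%, unpooled variance, and no outcome information from patients who drop out.

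Type I error is not in danger. One final test at the printed 2.0141 stays between 4.98% and 5.15% for any final count from 238 to 264. Recomputing the last boundary is good practice and costs little, but it does not repair a serious fault.

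**What to change.** 1. In the sample size section, either keep 264 and state that about 238 patients are expected to be evaluable, with power of about 79.6%, or correct the target to 134 per group (268 in total). Say whether the 10% refers to patients randomised.
2. In the group sequential section, define the final analysis as a single test of all randomised patients once the last has passed the 3-month visit. Recompute the last critical value at the actual count from the alpha left after the first two looks: about 2.012 at 238, 2.021 at 250 and 2.031 at 264.
3. In the abstract, announce two interim analyses (120 and 180 patients) and one final analysis, in line with the group sequential section and Table 2.

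The cost is a few sentences and one boundary calculation at the end, plus either four more patients or a marginally lower stated power.

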### Group sequential design and interim analysis

To allow for early stopping of the trial, a group sequential analysis is performed. The first of three interim analyses will be performed as soon as 120 patients (60 per group) have had their 3-month follow-up. Further interim analyses are planned after 180 and 240 patients (final analysis).

We will use a χ^2^-test to test the null-hypotheses. The analysis will be performed on the 'intention-to-treat' basis, i.e. patients will be analyzed in the groups to which they were randomized.

### Stopping rules

The randomization code will not be broken for the interim analyses, unless a stopping rule is met. At each interim analysis, the following stopping rules will apply:

1. A χ^2^-test demonstrates that one treatment is superior over the other (i.e. rejection of the null-hypothesis) OR,

2. If statistical significance cannot be likely reached with the maximum allowable number of patients for the study, which is set to 200 per arm (i.e. acceptance of the null-hypothesis).

Table 2 shows the threshold z-values for the χ^2^-test at each interim analysis. Boundaries for the interim analyses are calculated on the model developed by O'Brien & Fleming [26-32] (Figure 5).

**Figure 5 F5:**
[figure not shown]
boundaries and estimated example of the interim analysis.

**Table 2 T2:** Threshold z-values for the χ^2^-test at each interim analysis

**Interim analyses**	**Number of patients**	**Reject H_0 _if z ≥ **	**Accept H_0 _if z <**	**Reject H_0 _if p ≤**
1	120	-2.9626	2.9626	0.0031
2	180	-2.359	2.359	0.0183
3 = final analysis	240	-2.0141	2.0141	0.044

If a stopping criterion has not been reached, the trial will continue until the next interim analysis. If the trial is stopped after an interim analysis, all patients already enrolled in the trial will be followed up to the last planned visit.

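### Table 2's z columns cannot be applied as printed: they reject and accept H0 over the same range and leave no value of z at which the trial continues

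*Protocol article*

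**What the plan says.** The protocol article plans analyses at 120, 180 and 240 patients, the last being final, with O'Brien-Fleming boundaries and a χ² test. Table 2 gives two z thresholds and a p threshold for each look:

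| Look | Patients | "Reject H_0 _if z ≥" | "Accept H_0 _if z <" | Reject if p at or below |
|---|---|---|---|---|
| 1 | 120 | -2.9626 | 2.9626 | 0.0031 |
| 2 | 180 | -2.359 | 2.359 | 0.0183 |
| 3 (final) | 240 | -2.0141 | 2.0141 | 0.044 |

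Three other statements bear on how the table is to be used:

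- The sample size section fixes a two-sided test ("Considering a 0.05 two-sided significance level, a power of 80" per cent), and stopping rule 1 rejects H0 when either treatment proves superior.
- Stopping rule 2 accepts H0 only on a forward-looking condition: "If statistical significance cannot be likely reached with the maximum allowable number of patients for the study, which is set to 200 per arm".
- Directly below the table: "If a stopping criterion has not been reached, the trial will continue until the next interim analysis".

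**The concern.** A group sequential table has to divide the possible values of z at each interim look into stopping for a difference, continuing and, where there is a futility rule, stopping for no effect. Table 2 does not do this. The rejection inequality runs the wrong way for a negative threshold, so it takes in nearly all results, including no difference at all. The acceptance threshold at looks 1 and 2 equals the efficacy bound, so it is the complement of the upper rejection region and not a futility boundary.

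This matters because Table 2 is the only numerical decision rule in the document. The section on sample size re-estimation hands the interim analyses to an independent organisation and withholds other results from the investigators unless a stopping rule is met, so they are poorly placed to notice a misapplied bound. A rule that contradicts itself also leaves the stop-or-continue decision open to choice once the data are seen, which fixed boundaries are meant to prevent.

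**Working it through.** **Inputs**

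- Sample size section: two-sided alpha 0.05; power 80%; control rate 30% ("risk of occurrence of chronic pain without local anaesthetic infiltration of 30" per cent); 50% reduction, hence 15% on treatment; 120 per group.
- Group sequential section: looks at 120, 180 and 240 patients, giving information fractions t = 0.50, 0.75, 1.00.
- Table 2: absolute bounds 2.9626, 2.359, 2.0141.
- The 10% dropout allowance does not enter the boundaries.

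**1. Reproducing the plan's own figures**

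Use Lan-DeMets spending of O'Brien-Fleming type with 0.025 in each tail. Cumulative two-sided alpha at t is 4 × [1 − Φ(2.2414/√t)], where 2.2414 is the 0.9875 normal quantile. This gives 0.0031, 0.0193 and 0.0500. Solving for the bounds by recursive integration gives 2.9626, 2.3590 and 2.0141. The nominal p-values, 2 × [1 − Φ(c)], are 0.00305, 0.0183 and 0.0440. All agree with Table 2, and rejecting when |z| ≥ c has overall two-sided alpha 0.0500. (The classical O'Brien-Fleming bounds would be 2.863, 2.337 and 2.024, so the spending-function version was evidently used.)

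**2. The printed regions at look 1**

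- Reject: z ≥ -2.9626. Accept: z < 2.9626.
- Union: every z, so no value leads to continuation.
- Overlap: -2.9626 ≤ z < 2.9626, where both decisions apply. Outside this range one decision applies, but the trial still stops.
- z < -2.9626, an extreme result in one direction, is classed as acceptance only.

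Look 2 has the same structure with 2.359. At the final look, ending without continuation is proper, but the overlap remains.

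**3. Probabilities under H0 at look 1**

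- Rejection column alone: P(Z ≥ -2.9626) = Φ(2.9626) = 0.9985, against 0.0031 in the p column of the same row.
- Both decisions at once: Φ(2.9626) − Φ(-2.9626) = 0.997.

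**4. Probabilities at 30% against 15%, 60 per arm**

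Take z positive when treatment is better.

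- Unpooled: SE = √[(0.30 × 0.70 + 0.15 × 0.85)/60] = √(0.3375/60) = 0.075; mean of z = 0.15/0.075 = 2.00; P(z ≥ 2.9626) = 1 − Φ(0.9626) = 0.168.
- Pooled: SE = √(2 × 0.225 × 0.775/60) = 0.0762; mean of z = 1.967; P(z ≥ 2.9626) = 0.160.
- Exact Pearson calculation: 0.149.

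If the acceptance column is followed, the trial therefore stops for H0 at look 1 with probability 1 − 0.168 = 0.832 to 1 − 0.149 = 0.851, and power is 15 to 17%. The document does not fix the sign of z. With the opposite sign a benefit makes z negative, and the acceptance condition would be met almost with certainty.

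**5. With continuation restored**

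Reject if |z| ≥ c at each look, and otherwise continue at looks 1 and 2. Rejection probabilities by look at 30% against 15% with 120 per arm:

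| Variance | Look 1 | Look 2 | Final | Power |
|---|---|---|---|---|
| Unpooled | 0.168 | 0.372 | 0.260 | 0.800 |
| Pooled | 0.160 | 0.364 | 0.263 | 0.787 |

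This matches the stated 80%, so the intended design is sound and only the written z rule is at fault.

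**The case against.** The strongest reply is that the intended efficacy rule can be read off the page. The p column is right, the test is declared two-sided, rule 1 allows either treatment to win, and the sentence under the table provides for continuation. A competent statistician would infer |z| ≥ c and otherwise carry on, and would not declare superiority at z = 0 against a row requiring p ≤ 0.0031. On this view the 0.998 and the 16% come from two different and incompatible misuses of the table and are not properties of the design. The first column may also be a reversed inequality (z ≤ -c, the lower rejection limit) instead of a wrong sign, and Figure 5, not available in the text reviewed, may draw the regions correctly.

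Much of this stands. The magnitudes and p-values are correct, no alpha or sample size figure changes, and the two probabilities apply only to a literal reading. Wrong sign and reversed inequality cannot be told apart, but under either the printed column contradicts the p column.

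It does not rescue the acceptance column. The p column gives no acceptance threshold, so it cannot correct that entry. Even if a plus-minus or absolute-value sign were lost when the text was read from PDF, acceptance and rejection would still share one threshold at looks 1 and 2. That leaves no room for continuing, and it contradicts rule 2, which is not a fixed z cut-off.

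**Conclusion.** The concern holds. As printed, the two z columns of Table 2 overlap, exhaust all values of z, and contradict the p column, the continuation sentence and stopping rule 2. Literally applied at look 1, the rejection column has a type I error of 0.998 in place of 0.003. The acceptance column cuts power from the planned 80% to about 16% (range 15 to 17% by variance method). These sizes assume the design rates of 30% and 15%, 60 patients per arm at look 1, and z taken as positive for benefit. The fault is in how the rule is specified. The bounds themselves are right, and the intended design has alpha 0.0500 and power of 79 to 80%. Because these are the operative stopping thresholds, they must be corrected before any interim analysis is run.

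**What to change.** Replace the two z columns with one rule per look and keep the p column:

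| Look | Patients | Stop and reject H0 if | Otherwise |
|---|---|---|---|
| 1 | 120 | \|z\| ≥ 2.9626 | continue, unless stopping rule 2 (futility) is met |
| 2 | 180 | \|z\| ≥ 2.359 | continue, unless stopping rule 2 (futility) is met |
| 3 (final) | 240 | \|z\| ≥ 2.0141 | do not reject H0 |

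Delete the acceptance entries at looks 1 and 2, so that stopping for no effect before the final look can come only from rule 2. Add a note that z is the signed square root of the Pearson χ² statistic and say which direction is positive. The cost is a correction to one table; sample size, timing of looks and conduct are unchanged.
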